### Statistical analysis

Continuous variables will be summarized as mean ± standard deviation if normally distributed or as median (interquartile range) otherwise. Categorical variables will be presented as frequencies and percentages. Group comparisons will be performed using the *t*-test for normally distributed continuous variables, the Wilcoxon rank-sum test for non-normally distributed data, and the chi-square or Fisher’s exact test for categorical variables. To account for potential baseline imbalances, group differences in primary and secondary outcomes at week 7 will be evaluated using Analysis of Covariance (ANCOVA), with the respective baseline scores included as covariates.

Analyses will be performed on both the intention-to-treat (ITT) and per-protocol (PP) populations, with the ITT set serving as the primary analysis population. Missing data in the ITT population will be handled using multiple imputation. Safety will be assessed in all participants receiving at least one intervention session. Adverse events and complications will be analyzed using chi-square or Fisher’s exact tests.

Exploratory subgroup analyses according to baseline stroke severity (baseline NIHSS score) will be performed to explore potential heterogeneity of treatment effects. Because the study is not powered for subgroup analyses, these analyses will be considered exploratory and interpreted cautiously.

All statistical analyses will be conducted using R software (version 4.2.2; R Foundation for Statistical Computing, Vienna, Austria). All tests will be two-sided with a significance level of 0.05. Statisticians will remain blinded to group allocation throughout the process.

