### Randomization and blinding

Enrolled participants will be randomly assigned in a 1:1 ratio to either the ETT training group (receiving conventional rehabilitation combined with ETT training) or the sequential EECP-ETT training group (receiving conventional rehabilitation combined with sequential EECP followed by ETT training). The randomization sequence will be computer-generated by an independent statistician using SPSS software, employing a variable block randomization design. Randomization will not be stratified according to any baseline characteristics. To ensure strict allocation concealment, sequentially numbered, opaque, sealed envelopes will be utilized. Due to the physical nature of the interventions, blinding of participants and administering therapists is unfeasible. However, to minimize detection bias, all outcome assessors and data analysts will remain strictly blinded to the group assignments throughout the trial.

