### Clinical data collection

Comprehensive baseline data will be collected for all enrolled participants, encompassing the following categories:

Demographic characteristics: age, sex, height, and weight (with body mass index [BMI] calculated accordingly).

Stroke-related specifications: date of ischemic stroke onset, infarct location, history of reperfusion therapy (e.g., intravenous thrombolysis or mechanical thrombectomy), and related surgical interventions (e.g., decompressive craniectomy).

Comorbidities: presence of hypertension, diabetes mellitus, myocardial infarction, cardiomyopathy, and specific arrhythmias.

Current medications: use of antiplatelet agents, anticoagulants, statins, antihypertensive, and neurotrophic/neuroprotective agents.

Vital signs: body temperature, blood pressure, heart rate and rhythm, respiratory rate, and peripheral oxygen saturation.

Laboratory parameters: white blood cell count, neutrophil percentage, hemoglobin, platelet count, interleukin-6, C-reactive protein, procalcitonin, D-dimer, B-type brain natriuretic peptide, alanine aminotransferase, aspartate aminotransferase, serum creatinine, blood urea nitrogen, albumin, and prealbumin.

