### Outcomes

The outcome measures were selected to evaluate the potential clinical benefits of the sequential EECP-ETT strategy within a comprehensive rehabilitation program. As the proposed sequential intervention is intended to improve orthostatic tolerance and facilitate early verticalization, its potential benefits are expected to extend beyond immediate hemodynamic effects to multiple domains of functional recovery commonly affected after stroke. The primary outcome is neurological function at week 7, assessed by the NIHSS. NIHSS was selected as the primary endpoint because it comprehensively reflects overall neurological recovery, which is the ultimate goal of early stroke rehabilitation beyond immediate hemodynamic improvements. Secondary outcomes include the incidence of symptomatic OH, recorded continuously during all ETT training sessions throughout the 7-week intervention. OH is defined as a systolic blood pressure drop ≥ 20 mmHg, a diastolic drop ≥ 10 mmHg, or the onset of hypotensive symptoms within 3 min of tilting (30). Additional secondary outcomes, assessed at week 7 (Table 1), evaluate specific functional domains and hemodynamics, including motor function quantified by the FMA, balance function assessed by the BBS, swallowing ability via the MMASA, activities of daily living quantified by the BI, and noninvasive hemodynamic parameters, specifically cardiac index (CI), stroke volume (SV), and systemic vascular resistance index (SVRI).

**Table 1 tab1:** Outcome domains and measurement instruments.

**Outcome domain**	**Measurement instrument**	**T0**	**T1**
Primary outcome			
Neurological function	National Institutes of Health Stroke Scale	√	√
Secondary outcomes			
incidence of symptomatic orthostatic hypotension	Noninvasive blood pressure monitor and clinical observation	*	*
Motor function	Fugl-Meyer Assessment	√	√
Balance function	Berg Balance Scale	√	√
Swallowing function	Modified Mann Assessment of Swallowing Ability	√	√
Activities of daily living	Barthel Index	√	√
Noninvasive hemodynamic parameters	Thoracic electrical bioimpedance assessment system	√	√

T0 baseline, T1 post-intervention (week 7). *The incidence of symptomatic orthostatic hypotension is monitored continuously during each ETT training session rather than at discrete T0/T1 timepoints.

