### Sample size estimation

Since there is limited literature evaluating the synergistic effects of this specific sequential intervention, the sample size was calculated based on our unpublished preliminary pilot study involving 18 participants (9 in each group). The mean NIHSS score at the end of the trial was 7.99 ± 3.82 in the ETT training group and 5.28 ± 2.16 in the sequential EECP-ETT training group, giving an expected difference (*δ*) of 2.71 with a standard deviation (*σ*) of 3.82. With a two-sided significance level (*α*) of 0.05, power (1–*β*) of 90%, and equal allocation (1: 1), the required sample size for each group was calculated using the formula:

$$n=\frac{2{\left(z_{\alpha }+z_{\beta }\right)}^{2}*\sigma^{2}}{\delta^{2}}$$

This calculation indicated that 42 participants per group were required (84 in total). Allowing for a 20% dropout rate, 52 participants will be recruited per group, for a total sample size of 104.

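### The week-7 ANCOVA leaves out time since stroke onset, a small and avoidable loss of precision, and is not named as the single primary test

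*Protocol article*

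**What the plan says.** All references are to the protocol article.

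- **Outcomes:** "The primary outcome is neurological function at week 7, assessed by the NIHSS".
- **Statistical analysis, general rule:** group comparisons use the t-test for normal data and "the Wilcoxon rank-sum test for non-normally distributed data". No outcome or timepoint is named, and the rule is not limited to baseline tables.
- **Statistical analysis, week-7 rule:** the next sentence assigns ANCOVA to the primary and secondary outcomes at week 7, "with the respective baseline scores included as covariates". Its stated purpose is to deal with possible baseline imbalance.
- **Statistical analysis, remainder:** the ITT set is the primary population, with multiple imputation for missing data. "All tests will be two-sided with a significance level of 0.05". No test is labelled primary.
- **Participants:** stroke onset must be less than 3 months before entry. No lower limit is given.
- **Randomization and blinding:** "Randomization will not be stratified according to any baseline characteristics".
- **Clinical data collection:** baseline data for every participant include "date of ischemic stroke onset, infarct location, history of reperfusion therapy".

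**The concern.** Two patients with the same baseline NIHSS may enter the trial almost three months apart in their recovery. The protocol's own Discussion places the 7-week period in early subacute recovery, so time since onset is a natural candidate for predicting the week-7 score beyond the baseline score. It is not balanced by design and not in the model, although it can be computed for everyone. If it is prognostic, the treatment effect is estimated less precisely than the collected data allow.

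The second issue is in the same paragraph. The t-test/Wilcoxon rule is never made subordinate to the ANCOVA, and nothing says what happens if the week-7 NIHSS is non-normal. A later reader could not tell from the article alone which p-value decides the primary question if the two differ.

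**Working it through.** **1. The plan's own sample size.** Sample size estimation gives the pilot values: "The mean NIHSS score at the end of the trial was 7.99 ± 3.82 in the ETT training group and 5.28 ± 2.16". Hence δ = 7.99 − 5.28 = 2.71. The planning SD is 3.82, with two-sided α 0.05 and power 90%.

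n per arm = 2 × (1.960 + 1.282)² × 3.82² / 2.71² = 41.76, rounded up to 42.

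The stated 42 per arm is reproduced. The formula is for two unadjusted means, so any useful covariate adds power beyond the plan. Unadjusted power at 42 per arm is 90.2%.

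**2. What time since onset could add.** The documents give neither of the two quantities needed, so both are assumed:
- correlation ρ between baseline and week-7 NIHSS: 0.5 or 0.7 in this step;
- share R² of the variance left after baseline NIHSS that time since onset explains: 0.02 to 0.15.

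Adjusted SD = 3.82 × √(1 − ρ²) × √(1 − R²). For ρ = 0.5 and R² = 0 this is 3.308.

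Power = Φ(δ / (SD × √(2/42)) − 1.96). At half the planned effect (δ = 1.355), ρ = 0.5 and R² = 0: 1.355 / (3.308 × 0.2182) = 1.877, and Φ(1.877 − 1.960) = 46.7%.

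| R² | SE factor √(1 − R²) | SE reduction | Power, δ = 1.355, ρ = 0.5 | Power, δ = 1.355, ρ = 0.7 | Power, δ = 2.71, ρ = 0.5 |
|---|---|---|---|---|---|
| 0 (baseline NIHSS only) | 1.000 | – | 46.7% | 62.4% | 96.4% |
| 0.02 | 0.990 | 1.0% | 47.5% | 63.3% | 96.7% |
| 0.05 | 0.975 | 2.5% | 48.6% | 64.6% | 97.1% |
| 0.10 | 0.949 | 5.1% | 50.7% | 67.0% | 97.7% |
| 0.15 | 0.922 | 7.8% | 53.0% | 69.5% | 98.3% |

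Baseline NIHSS takes most of the gain: at δ = 2.71 and ρ = 0.5 it lifts power from 90.2% to 96.4%, and time since onset adds 0.3 to 1.9 points. At ρ = 0.7 the baseline-only figure is already 99.5%.

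**3. What the assumed R² means on the NIHSS scale.** Assume onset times are uniform over 13 weeks (SD 13/√12 = 3.75 weeks) and independent of baseline NIHSS. At ρ = 0.5 the variance left is 3.82² × 0.75 = 10.94. The slope for a given R² is √(R² × 10.94) / 3.75. That gives 0.12 points per week for R² = 0.02 and 0.34 for R² = 0.15. A reader with a view on that slope can place the trial in the table.

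**4. If either test could be claimed.** Simulation with 42 per arm, normal baseline and outcome, and ANCOVA on baseline only as planned; 10,000 runs under no effect and 4,000 at each effect size.

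| Assumed ρ | Type I, t-test alone | Type I, ANCOVA alone | Type I, either significant | Tests disagree, δ = 2.71 | Tests disagree, δ = 1.355 |
|---|---|---|---|---|---|
| 0.5 | 4.6% | 4.8% | 7.0% | 7.5% | 17.5% |
| 0.7 | 4.6% | 4.9% | 7.9% | 9.5% | 32.0% |
| 0.8 | 4.9% | 5.2% | 8.9% | 11.2% | 45.0% |

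Each test alone holds its level within simulation error. The excess comes only from being free to choose.

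**The case against.** **Omitting a covariate is not an error.** This stands. Under randomization the baseline-only ANCOVA is unbiased, and chance imbalance in onset time is already part of its standard error. A reader might infer that an unstratified trial with a wide onset window gives a distorted estimate. The documents do not support that. With uniform onset times and 52 per arm, the 95% limit of chance imbalance is 1.96 × 3.75 × √(2/52) = 1.4 weeks. At an assumed 0.1–0.3 points per week that is 0.14–0.43 points, against a planned unadjusted 95% half-width of 1.96 × 3.82 × √(2/42) = 1.63 points.

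**The gain rests on assumed values.** Also true. The documents give no onset distribution, slope or R², and a gain worth dozens of patients cannot be claimed. A slope of 0.1 points per week gives a variance of (0.1 × 3.75)² = 0.14. Against a remaining variance of 10.94 (ρ = 0.5) or 5.25 (ρ = 0.8), that is an R² of only about 1–3%. Nor do the documents supply a case for adding age as well.

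**ANCOVA is plainly the week-7 method.** Largely right. It is the only method tied to the primary outcome, and a specific sentence normally overrides a general one. A reader might infer that the plan prescribes two competing primary tests and so runs at 7–9% type I error. That needs selective claiming, which the plan does not describe, and the analysts are to be blinded.

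Still, the general rule cannot be only for baseline tables. Symptomatic orthostatic hypotension is a secondary outcome with no baseline score, so the chi-square/Fisher part of that same rule is the only method left for it. The rule therefore reaches outcomes, and its limits are unstated.

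**An analysis plan may settle this.** It may; it is not shown. The point is about what the article states: a covariate set fixed to one variable, and a test rule with no stated boundary.

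**Conclusion.** The point holds in a modest form. Restricting the week-7 model to the baseline score is a missed efficiency gain of about 1–8% of the standard error, for an assumed R² of 0.02–0.15. It does not bias the estimate or threaten the stated sample size. The gain matters mainly if the true effect is well below the pilot's: at half of 2.71, with ρ = 0.5, power is higher by 0.8 to 6.3 percentage points.

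The choice of test is an ambiguity, not a contradiction. ANCOVA is the better-supported reading. The 7–9% type I error (assumed ρ 0.5–0.8) is what the wording fails to rule out, not what it plans.

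**What to change.** Before the analysts are unblinded, state in the protocol or analysis plan that the single primary analysis is ANCOVA of week-7 NIHSS on arm, baseline NIHSS and time since onset, in the ITT set with multiple imputation. Say that t-test and Wilcoxon results for week-7 scores are supportive only, and that observed normality does not change the primary method. Fix the form of time since onset at the same time (for example, days from onset to randomization, entered linearly), and include it in the imputation model.

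The cost is one sentence and one model degree of freedom: with 84 evaluable patients, residual degrees of freedom go from 81 to 80. No new data or patients are needed. The Trial status section reports that recruitment is ongoing, with the trial expected to end by December 2026, so there is time to make the change.

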### Data collection and management

Baseline demographic and clinical characteristics will be recorded solely at enrollment, whereas functional assessments will be evaluated at both baseline and the end of the 7-week intervention period. Hemodynamic parameters (blood pressure, heart rate, mean arterial pressure, and oxygen saturation) will be monitored and documented before, during, and after each intervention session. All clinical data will be entered into standardized electronic Case Report Forms (eCRFs) by trained personnel. To ensure data integrity, a secure Electronic Data Capture (EDC) system will be utilized. Data quality will be guaranteed through real-time automated logic and range checks, supplemented by a double-data entry protocol and routine cross-validations by an independent data manager. To strictly protect patient confidentiality, all participants will be de-identified using unique study-assigned codes. The EDC system incorporates a comprehensive audit trial, logging all modifications with timestamps and operator identifications to ensure complete traceability. All documentation and data storage will rigorously comply with institutional and national data protection regulations.

## Discussion

Early mobilization via ETT-mediated verticalization is an integral component of stroke rehabilitation, particularly for patients with severe motor deficits (31, 32). Transcending passive positioning, verticalization serves as a potent physiological stimulus that activates the reticular activating system to enhance arousal, heighten proprioceptive input, and facilitate orthostatic adaptation (33–35). Additionally, ETT training is a key clinical strategy to mitigate the sequelae of prolonged bed rest, such as cardiopulmonary deconditioning and venous stasis (36). However, its clinical utility is frequently constrained by OH. This failure of autonomic adjustment to gravitational stress often leads to training interruptions, thereby limiting mobilization intensity and potentially delaying functional recovery (37). Addressing this orthostatic barrier is therefore a clinical priority for optimizing rehabilitation outcomes.

Enhanced external counterpulsation offers a physiological solution to this dilemma. Building upon its established utility in cardiology, EECP theoretically establishes a ‘hemodynamic priming’ state in stroke patients through its mechanisms of diastolic augmentation and enhanced venous return (38–40). By increasing shear stress and improving endothelial function, EECP actively redistributes pooled blood from the splanchnic and lower-limb prior to gravitational challenge (41, 42). We hypothesize that this pre-conditioning stabilizes systemic vascular resistance and maintains sustained cerebral perfusion pressure during subsequent ETT training. EECP may enhance verticalization tolerance in terms of both duration and angle, thereby ensuring patients receive the optimal therapeutic intensity required for early recovery.

This trial is designed to provide preliminary clinical evidence regarding the sequential integration of these two modalities within a sequential framework. Unlike isolated therapies, the “EECP followed by ETT” strategy targets a synergistic effect: EECP optimizes the hemodynamic substrate, while ETT training capitalizes on this stability to maximize motor and neurological relearning. If this strategy successfully improves orthostatic tolerance and enables patients to tolerate earlier and more intensive verticalization training, benefits may extend beyond overall neurological recovery to multiple functional domains. Early verticalization may provide weight-bearing, proprioceptive input, and postural activation of the affected limb, thereby facilitating motor recovery and balance, which will be evaluated using the FMA and BBS. In addition, improved overall neurological recovery and earlier comprehensive rehabilitation may also contribute to better swallowing function and greater independence in activities of daily living, as assessed by the MMASA and BI. Because orthostatic intolerance and impaired mobilization may occur across a broad spectrum of patients during early stroke rehabilitation, the present trial does not restrict enrolment according to baseline stroke severity. Although patients with greater mobility impairment may derive greater benefit from improved orthostatic tolerance during verticalization training, patients with milder stroke may also benefit through enhanced participation in early rehabilitation. This study will not only verify the safety and feasibility of this integrative approach but also elucidate whether stabilizing hemodynamics correlates with superior functional outcomes. If successful, this sequential protocol could potentially refine the standard of care by defining a safe, accelerated pathway for early mobilization, thereby improving the management of bedridden ischemic stroke patients.

Several limitations to this study should be acknowledged. First, as a single-center randomized controlled trial, the generalizability of our findings to diverse clinical settings or more severe stroke populations may be limited. Future multi-center studies with larger, more heterogeneous cohorts are warranted to validate the efficacy of this sequential protocol. Second, while outcome assessors and data analysts will be blinded, the inherent nature of physical interventions such as EECP and ETT training precludes the blinding of participants and therapists, which may introduce potential performance bias. To mitigate this, standardized treatment protocols and objective outcome measures have been strictly implemented. Finally, the 7-week follow-up period focuses primarily on early subacute recovery; thus, the long-term sustainability of the observed functional improvements and their impact on chronic functional status remain to be elucidated in subsequent longitudinal studies.

### Trial status

Patient recruitment is ongoing. This study adheres to protocol version 1.0. Following approval by the ethics committee, the finalized protocol was distributed to the study center managers and archived online to ensure transparency and systematic record-keeping. The first patient was enrolled in July 2024, and the trial is anticipated to be concluded by December 2026.
